## Statistical considerations

### Primary and secondary outcomes

All analyses will be conducted according to the intention-to-treat principle. Baseline characteristics will be compared by treatment group. Effects of treatment on the primary study endpoint (complete healing of the index ulcer at 6 months) will be estimated with the use of unadjusted logistic regression with last observation carried forward for those lost to follow-up. All *P*-values will be two-sided and *P*-values less than 0.05 will be considered to indicate statistical significance. Multiple logistic regression will be applied to adjust for prognostic factors such as vascular insufficiency and site of DFU (fore-, mid- or hind foot) which are strongly correlated with the outcome (*r* ≥ 0.3) [25, 26]. Binary secondary outcomes at 12 months will be analysed similarly. For continuous secondary outcomes, change score analysis that determines treatment effect based on the difference between baseline and post treatment score (basic adjustment) will be undertaken. Multiple linear regression adjusting for i) the baseline value of the outcome variable in the model (model 1), and ii) model 1 + adjustment for prognostic baseline factors (model 2) will be undertaken. Data will be analysed using IBM SPSS Statistics 25.

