## Background

One Australian loses a limb every 3 h as a direct consequence of diabetes related foot disease, usually due to an infected diabetic foot ulcer (DFU) [1, 2]. That amounts to around 8000 lower extremity amputations (LEA) undertaken in Australia each year [3, 4]. In Western Australia (WA) alone, more than 200 major (above the ankle) LEA are performed annually and recurrent minor (below the ankle) amputations in patients with Type 2 diabetes (T2DM) are increasing by about 3.5% per annum [5]. There has been a 30% increase in diabetes-related amputations, largely related to increasing diabetes prevalence [6] in Australia over the past decade and 8% of diabetes-related deaths are attributable to foot complications [1, 2, 7]. These poor outcomes have persisted despite increasing awareness of the medical, economic and social burden of diabetic foot complications [8]. The economic costs and mortality rates exceed that of many common cancers; the 5-year mortality rate of patients with diabetic foot infections is ~ 50% [9–12]. The estimated economic burden in Australia may exceed $1.5 billion, with DFU accounting for 33% of diabetes related costs [13]. Poor outcomes associated with DFU are disproportionately high in the Australian Indigenous population [14]. A recently published systematic review has found that Aboriginal and Torres Strait Islander Australians are 3–6 times more likely to experience a diabetes related foot complication than non-Aboriginal Australians [15]. Therefore there is an urgent need to test interventions to improve healing time, reduce recurrent ulceration and the incidence of LEA in patients with DFU whilst optimising function and quality of life.

In addition to in-patient services required when the DFU becomes limb or life threatening, most of the morbidity and economic burden of DFU is carried by public sector outpatient services. Wound healing time is a key cost driver and influences the overall cost-benefit analysis for any DFU intervention [16]. It is estimated that the mean healing time for a DFU managed without amputation is 6 months, rising to 12 months if an amputation is required [17, 18]. The outpatient component of management accounts for 71% of the total costs associated with DFU and suggests that reductions in the time to healing are likely to have major benefits for direct costs, particularly related to home nursing visits, dressings and outpatient appointments.

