## Study design

This study is a prospective, randomised, open label trial powered for superiority. Local and international data informed sample size calculations indicating that, at present, 45% of patients with DFU will achieve complete healing at 6 months [17, 18, 21]. We estimate that 136 (with continuity correction) patients are required to have 80% chance of detecting, at the 5% level of significance, an increase in the primary outcome measure from 45% in the control group to 70% in the spray-on skin group [19]. To account for drop-outs, we will aim to recruit 150 participants in total.

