### Primary outcome

The primary outcome for the trial will be a dichotomous outcome of complete healing of the index ulcer at 6 months as defined by full epithelialisation, after debridement of callus, lasting for at least 2 weeks. Primary outcome arbitration at the interim analysis and at the final analysis will be performed using the database, wound dimension and clinical images assessed by two independent senior clinicians (not investigators) blinded to the intervention. Discordant outcome assessments will be resolved by consensus.

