### Follow up measurements

Patients will be followed up at predefined time points. This will coincide with routine outpatient visits ordinarily scheduled at 4, 10, 18, 26, 39 and 52 weeks from randomisation with phone consultations every fortnight to determine total ‘ulcer-free’ days following healing. At each scheduled visit, the wound will be assessed in terms of location (exact; forefoot vs. hind- and mid-foot), depth, dimensions, wound volume and wound area (as measured by Silhouette™ [Aranz Medical]), wound quality (patchy vs. confluent, % epithelialisation), probe to bone test and photography. Both feet will be assessed for new wounds. Blood tests will be (lipids, C-reactive protein, full blood examination and renal and liver function tests) will be performed as clinically indicated, but an HbA_1c_ will be measured at 3, 6 and 12 months to determine the change from recruitment. All patients will receive standard care related to off-loading, ongoing diabetes management and infection management as per the usual management protocol of the multi-disciplinary foot ulcer teams. In addition to baseline, an EQ-5D-5 L [22] will be performed at 26 and 52 week visits to ascertain change in health-related quality of life [24]. The primary outcome will be assessed at the 26-week visit.

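### Last observation carried forward as the primary rule for 26-week healing counts most early dropouts as not healed, so it can bias the comparison when dropout differs by arm and dilutes a true effect when it does not

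*Protocol article*

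**What the plan says.** Under *Primary and secondary outcomes* in the statistical section, the article states the analysis principle ("All analyses will be conducted according to the intention-to-treat principle") and then the primary method: the effect on healing "will be estimated with the use of unadjusted logistic regression with last observation carried forward for those lost to follow-up". The *Primary outcome* section defines healing as "full epithelialisation, after debridement of callus, lasting for at least 2 weeks". *Follow up measurements* fixes the time ("The primary outcome will be assessed at the 26-week visit") and lists clinic visits "scheduled at 4, 10, 18, 26, 39 and 52 weeks from randomisation". The visits from which a status can be carried to week 26 are therefore weeks 4, 10 and 18, plus baseline, when the ulcer is open.

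*Study design* describes an open-label trial that assumes 45% healing in control and 70% with spray-on skin. It raises the sample from 136: "To account for drop-outs, we will aim to recruit 150 participants in total". On later binary outcomes the statistical section says only "Binary secondary outcomes at 12 months will be analysed similarly".

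**The concern.** Carrying the last observation forward (LOCF) assumes that a patient's status would not have changed after the last visit. For this endpoint the status is expected to change. The healed share is zero at randomisation and is planned to reach 45% or 70% by week 26. The *Background* says "the mean healing time for a DFU managed without amputation is 6 months", so many ulcers that will heal are still open at weeks 4, 10 and 18. Coding such a patient as not healed contradicts the assumptions behind the sample size.

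The rule can also err the other way. A patient closed at week 18 and then lost is counted as healed at week 26, although re-ulceration is common enough to be a secondary outcome.

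Two things follow. If one arm loses more patients, its healing rate is pushed down further and part of the difference is an artefact. If the arms lose equal shares, a real effect is diluted, because the arm that heals more has more to lose. The intention-to-treat principle keeps every patient in the denominator, but it does not make the carried-forward value right.

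**Working it through.** **The plan's own figure.** For 45% v 70%, 80% power and two-sided 5%, with mean rate 0.575:

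n = [1.960·√(2·0.575·0.425) + 0.842·√(0.45·0.55 + 0.70·0.30)]² / 0.25² = 60.2, so 61 per arm.

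With continuity correction: (60.2/4)·[1 + √(1 + 4/(60.2·0.25))]² = 67.95, so 68 per arm and 136 in total, as stated. The dropout allowance is 14/150 = 9.3%. Without dropout, 75 per arm gives 88% power (normal approximation, no continuity correction).

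**Assumptions, not in the article.** Allocation is 1:1 with 75 per arm. Healing has a constant hazard matched to 45% and 70% at week 26. Dropout is unrelated to outcome and uniform over 26 weeks. Status is known only at clinic visits.

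**Share healed at each visit:** F(t) = 1 − (1 − p)^(t/26).

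| Last visit seen | Share of dropouts | Control (p = 0.45) | Treated (p = 0.70) |
|---|---|---|---|
| Baseline | 4/26 | 0 | 0 |
| Week 4 | 6/26 | 0.088 | 0.169 |
| Week 10 | 8/26 | 0.205 | 0.371 |
| Week 18 | 8/26 | 0.339 | 0.565 |

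Share of dropouts coded healed:
- Control: q = (6·0.088 + 8·0.205 + 8·0.339)/26 = 0.188, against 0.45 assumed.
- Treated: q = (6·0.169 + 8·0.371 + 8·0.565)/26 = 0.327, against 0.70 assumed.

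**Observed rate under LOCF with dropout d:** p − d·(p − q). The shortfall per unit of dropout is 0.262 when p = 0.45 and 0.373 when p = 0.70.

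- *Equal 9.3%, planned effect.* Control 0.45 − 0.093·0.262 = 0.426; treated 0.70 − 0.093·0.373 = 0.665. The difference is 24.0 points instead of 25, and power is about 85% instead of 88%.
- *14% control v 4.7% treated (about 9.3% overall), no true effect.* (0.14 − 0.047)·0.262 = +2.4 points; two-sided error 6.0%.
- *20% control v 5% treated (12.5% overall, above the plan), no true effect.* 0.15·0.262 = +3.9 points. Two-sided error is 7.8% by normal approximation and 8.6% in simulated trials.
- *5% control v 20% treated, planned effect.* Control 0.45 − 0.05·0.262 = 0.437; treated 0.70 − 0.20·0.373 = 0.625. The difference is 18.9 points, with power 64%.

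**Sensitivity to the assumptions.** Suppose instead that the last visit is spread equally over baseline and weeks 4, 10 and 18. The first result is then for constant hazard; the one in brackets is for linear healing from week 4.

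- 14% v 4.7%, no effect: +2.7 (+3.2) points, error 6.3% (6.9%).
- 20% v 5%, no effect: +4.4 (+5.2) points, error 8.4% (9.9%).
- Equal 9.3%, planned effect: 23.8 (23.2) points, power 84% (82%).
- 5% v 20%, planned effect: 18.0 (15.9) points, power 60% (50%).

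For 20% v 5% with no effect and constant hazard, the bias is 1.7 points if every dropout is last seen at week 18, and 6.75 points if every dropout is last seen at baseline.

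**The case against.** **Unequal dropout is not predicted.** Nothing in the article says that controls will leave sooner, and the entry criteria select patients who can be followed up. A reader might infer that LOCF is biased whenever dropout differs. That is too strong. There is no bias if the lost patients would not have healed, or had healed and stayed healed, and opposite errors can cancel. This stands, and it is why the point says *can*.

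**The damage is modest at the planned loss.** A reader might take 20% v 5% as the expected case, but it exceeds the 9.3% allowance. With equal 9.3% loss and no true effect there is no bias, and under the planned effect power stays above 80%. This also stands, and it limits the size of the point.

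**Fortnightly phone contact and blinded outcome arbitration are planned.** If calls could supply the last status, the bias falls to +3.3 points (error 6.9%) for 20% v 5%, and to +2.1 points (5.7%) for 14% v 4.7%. But the stated purpose of the calls is to count ulcer-free days after healing, and a call is not a wound examination. Blinded arbitrators cannot recover an outcome that nobody saw. The problem is reduced at most, not removed.

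**Twelve-month outcomes.** A reader might infer that lost patients will be coded alive, unamputated and not re-ulcerated. The sentence "Binary secondary outcomes at 12 months will be analysed similarly" directly follows the one on multiple logistic regression and may refer only to the regression. Deaths and major amputations also have their own reporting route. The extension is a possible reading, not an established fault.

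**An analysis plan may say more.** It may well add sensitivity analyses, so their absence here is not a fault. Nor does the article suggest that losses by arm would go unreported. The choice of LOCF as the primary rule, however, is fixed in this document.

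**Conclusion.** The point holds for the choice of LOCF as the primary rule. It assumes no change after the last visit in an endpoint that the plan itself expects to rise from 0% to 45% or 70%, and in the illustration it codes about 19% and 33% of dropouts as healed.

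At the planned 9.3% overall loss, the cost is about one point of effect and three points of power if dropout is equal. If dropout splits 14% to 4.7% with no true effect, it is about 2.4 points of false benefit and 6% two-sided error. Beyond the planned pattern it grows: for 20% v 5%, about 3.9 points and an error of about 8 to 8.5%; for the reverse split under the planned effect, about 19 points and 64% power.

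The direction of the argument is secure. The sizes rest on assumed healing curves, dropout timing and dropout by arm, none of which the article gives. This is a change that should be made, not a flaw that invalidates the trial.

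**What to change.** Before any unblinded analysis, including the interim look that can stop the trial:

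1. Replace LOCF for the primary endpoint with multiple imputation by arm, using baseline covariates and the serial Silhouette area and volume, percentage epithelialisation and visit status already collected.
2. State that death, or amputation of the index site, before week 26 counts as not healed, so that these outcomes are defined and not imputed.
3. Support this with a tipping-point analysis that varies the healing rate among missing patients separately in each arm. Counting all missing patients as not healed should not be the main check, because it does not remove bias from unequal dropout. With no true effect and 20% v 5% it gives 0.45·0.15 = 6.75 points, against 3.9 for LOCF.
4. Clarify the sentence on 12-month binary outcomes. If it is meant to extend LOCF to mortality, amputation and re-ulceration, analyse these with censoring at last contact instead.

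The cost is analysis wording and modest programming, with no new data. Multiple imputation relies on a missing-at-random assumption that the data cannot confirm; the tipping-point analysis shows how far that assumption would have to fail to change the conclusion.

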## Discussion

There are substantial barriers to undertaking randomised controlled trials in patients with DFU. Significant heterogeneity in lower limb vascular supply, ulcer location and size, long-term diabetes control, infection extent, antibiotic efficacy, adherence to offloading and psychosocial issues are all factors that affect healing and may compromise the validity of testing a novel intervention to improve cure rates in this group. Restricting entry criteria may reduce heterogeneity in the trial participants, but places limits on generalisability of the results to other patients outside this group. For example, excluding patients with established osteomyelitis in the ‘SIDESTEP’ trial comparing ertapenem with piperacillin-tazobactam for diabetic foot disease limited generalisability to patients with this common complication [29].

In the case of the spray on skin intervention for the present trial, the goal was to maximise generalisability to as many patients with a DFU at ‘moderate’ risk of delayed healing. Because the additional costs are likely to be sensitive to the cost of ReCell®, smaller wounds with a high likelihood of healing, were not a suitable application for this intervention. Such wounds would include a transphalangeal amputation site in a patient with good blood supply. Likewise, limiting the intervention to a salvage therapy for wounds with an extremely high chance of clinical failure would also compromise the chances of demonstrating success.

Finding the balance between patient heterogeneity, prior knowledge about likelihood of success and the subsequent generalisability of the trial results is difficult and may have implications for the appropriate sample size calculations. In this trial, healing rates greater than 45% in the standard care arm from published data may not necessarily reflect outcomes for this type of ulcer in our tertiary multidisciplinary unit.

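### The covariates of the adjusted healing model are an open list tied to an unclear r ≥ 0.3 criterion; a short closed list named in advance would be better

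*Protocol article*

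**What the plan says.** Under Statistical considerations (Primary and secondary outcomes), the effect on the primary endpoint "will be estimated with the use of unadjusted logistic regression". The endpoint is a "dichotomous outcome of complete healing of the index ulcer at 6 months". The same paragraph adds a multiple logistic regression to "adjust for prognostic factors such as vascular insufficiency and site of DFU (fore-, mid- or hind foot) which are strongly correlated with the outcome". A bracket gives the strength as r ≥ 0.3, and two references follow. Binary secondary outcomes at 12 months are to be handled in the same way.

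Study design sizes the trial for a rise "from 45% in the control group to 70% in the spray-on skin group", "at the 5% level of significance", with 80% power: 136 patients with continuity correction, and 150 to be recruited. The Randomisation section names no stratification factor.

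**The concern.** Two factors are named, but only as examples, and membership of the list is tied to correlation with the outcome. The sentence does not say where that correlation comes from. If it is computed in the trial data, the adjusted model for the primary endpoint and the binary secondary outcomes is settled only once outcomes are known, in an open-label trial. Different samples, or different analysts, would then adjust for different factors.

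The criterion also fits one of its own examples poorly. Ulcer site has three nominal levels in this sentence, and a single r is not defined for such a factor. Follow up measurements records location as forefoot against mid- and hindfoot, which would allow one, but the article does not say which coding the rule uses.

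There is an efficiency side as well. The Discussion points to "Significant heterogeneity in lower limb vascular supply, ulcer location and size" among the things that affect healing. Baseline data on these are available, yet the primary model uses none of them.

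**Working it through.** **1. The plan's own sample size.** Inputs from Study design: "45% of patients with DFU will achieve complete healing at 6 months" as the control rate, 70% as the target, α = 0.05, power 80%. From the statistical section: P "values will be two-sided". Equal allocation is assumed (two arms, blocks of 2, 4 or 8).

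With p̄ = 0.575 and d = 0.25:

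n = [1.96·√(2·0.575·0.425) + 0.8416·√(0.45·0.55 + 0.70·0.30)]² / 0.25² = (1.370 + 0.569)² / 0.0625 ≈ 60.2, so 61 per arm.

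With continuity correction: (n/4)·[1 + √(1 + 4/(n·d))]² = 15.05 × (1 + 1.125)² ≈ 67.95, so 68 per arm and **136** in total. The stated figure reproduces.

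**2. Power of the unadjusted test as planned.** Without the correction, power = Φ[(d·√n − 1.370)/0.676].
- 68 per arm: Φ(1.022) = 84.7%.
- 75 per arm: Φ(1.175) = 88.0%.

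Both exceed 80%.

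**3. How r ≥ 0.3 behaves if it is a screen on trial data.** By Fisher's z, P(r observed ≥ 0.3) = 1 − Φ{[atanh(0.3) − atanh(ρ)]·√(n − 3)}, with n = 150 and √147 = 12.12.
- ρ = 0.30: 1 − Φ(0) = 50%.
- ρ = 0.25: 1 − Φ(0.0541 × 12.12) = 1 − Φ(0.66) = 26%.
- ρ = 0.20: 1 − Φ(0.1068 × 12.12) = 1 − Φ(1.29) = 10%.

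The threshold is strict. For a binary factor with 50% prevalence and overall healing of 57.5%, r = 0.3 needs a healing difference of 0.3 × √(0.575 × 0.425)/√0.25 ≈ 0.297, about 30 percentage points.

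**4. What selection and adjustment do to the treatment test.** Simulation with N = 136, 1:1 allocation, marginal healing 45% and 70%, binary covariates at 40% prevalence, and 4,000 runs per scenario. The covariate log-odds are assumptions, because the article gives none. The selected model keeps covariates with in-sample |r| ≥ 0.3.

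| Covariates (log-odds) | True r | Chance each is kept | Power: unadjusted | Power: fixed list | Power: selected |
|---|---|---|---|---|---|
| Two (0.8 each) | 0.17 | 6% | 85.3% | 87.7% | 85.5% |
| Two (1.3 each) | 0.25–0.26 | 30% | 84.6% | 89.5% | 86.2% |
| Five (1.3, 0.8, 0.5, 0.5, 0) | 0.27, 0.16, 0.10, 0.10, 0 | 33%, 4%, 1%, 1%, 0% | 83.7% | 88.5% | 84.6% |
| Two (1.8 each) | 0.32 | 63% | 84.6% | 92.5% | 89.8% |

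The gain of the fixed list over the unadjusted model is 2.4, 4.9, 4.8 and 7.9 points.

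With 45% healing in both arms, type I error was 4.6–4.8% unadjusted, 4.8–5.2% with the fixed list and 4.6–4.8% with selection. The Monte Carlo standard error is √(0.05 × 0.95/4000) ≈ 0.3 points, so none shows inflation.

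**The case against.** The strongest reply is that the sentence need not describe a screen at all. It names factors, describes them as strongly correlated with healing, and cites references; it may simply report what is already known. A reader might infer that covariates enter only if they correlate with this trial's own outcome, but the article says neither. This stands, and the figures in step 3 apply only under the screening reading. It does not remove the point, because the wording permits either reading and the list is open under both.

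Three other strong readings are not supported:
- **A faulty primary test.** Covariate choice cannot touch the unadjusted model, and simulated selection left type I error near 5%.
- **A shortfall in power.** The trial was sized for the unadjusted comparison and reaches its target. An unadjusted primary analysis is a legitimate choice, and no stratification factor is named that the model would have to include.
- **Exclusion of negatively related factors.** Taken literally, r ≥ 0.3 would bar a factor that lowers healing. But the sentence itself names vascular insufficiency as qualifying, so magnitude is evidently meant, and the sign depends on coding.

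It can also be said that a full covariate list belongs in an analysis plan that is not shown. That is fair, and the absence of a complete list is not the point. The point is the criterion that the article does state.

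**Conclusion.** The point holds in a limited form. The article defines its adjusted model by an open list and a correlation threshold whose source is unclear. If the threshold is applied to trial data, a moderately prognostic factor enters or drops out largely by chance, and the adjusted estimates for the primary endpoint and the binary secondary outcomes become unstable. If it describes prior evidence, the remaining fault is the open list.

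The primary result as planned is valid and adequately powered. The cost of leaving baseline data out of it is a forgone gain of about 2 to 8 power points. That range rests on assumed covariate effects (strongest true r per scenario about 0.17 to 0.32). The upper end needs two independent factors that each correlate at about 0.3 with healing, which nothing in the article establishes.

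**What to change.** Delete the r ≥ 0.3 criterion. Name in advance, from prior knowledge and before outcomes are seen, a short closed list of baseline covariates that are already collected, each with its coding: for example log ulcer area, site as forefoot against mid/hindfoot, and baseline vascular status. Use that list in the logistic model for the primary endpoint. Preferably make this the primary analysis and report a covariate-standardised risk difference, which keeps the marginal effect; keep the unadjusted model as supportive. Use the closed list for the binary secondary outcomes too.

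The cost is small. No new data and no change in sample size are needed. At the design rates, 150 × 0.575 ≈ 86 healed and 64 unhealed patients are expected, which supports a model with a handful of parameters. There are two consequences to state: the adjusted odds ratio is conditional rather than marginal, and the interim analysis must say which model it uses, since its sample size too is calculated for a comparison of two healing proportions.

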### Study population

The study population will be screened from patients attending the Fiona Stanley (FSH) or Royal Perth Hospital (RPH) inpatient or outpatient multidisciplinary foot units during the recruitment period. The primary ulcer requiring treatment will be considered the index ulcer for enrolment. The site of the index ulcer will be defined at enrolment and categorised as either being fore-, mid- or hindfoot. During the lead-in phase, the wound bed preparation will be standardised prior to randomisation. Recruitment will occur over an 18-month period and participants followed for 12 months.

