### Secondary outcomes

Secondary outcomes include: i) index ulcer free days at 12 months, ii) time to full epithelialisation of the index ulcer, iii) trajectory of wound healing of the index ulcer (defined as volume and measured using Silhouette™), iv) major adverse events, v) any minor or major lower limb amputation, vi) all-cause mortality, vii) re-ulceration of the index ulcer, viii) the development of any new ulcers ix) total costs of inpatient and outpatient costs (see economic analysis, below), x) readmission to hospital and xi) health-related quality of life (as measured by EQ-5D-5 L) [22].

The definitions for secondary outcomes are consistent with international guidelines [23]. Re-ulceration is defined as healing of index ulcer followed by subsequent ulceration with loss of epithelialisation at the same location. A minor amputation is an amputation below the ankle including toe, metatarsal-phalangeal and midfoot amputations. A major amputation is an amputation above the ankle including below knee and above knee amputations. New onset infection includes infections that have commenced during the preceding 2 weeks, including existing ulcers that have never previously been infected.

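### Carrying the last observation forward for death, amputation, readmission and new ulcers scores participants who leave early as event-free to month 12, so absolute risks are recorded too low

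*Protocol article*

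**What the plan says.** Under Statistical considerations, Primary and secondary outcomes, the protocol article estimates the effect on 6-month healing by "unadjusted logistic regression with last observation carried forward for those lost to follow-up". After a sentence on covariate adjustment it adds: "Binary secondary outcomes at 12 months will be analysed similarly". The only other route described there is change scores and linear regression for continuous outcomes. The section names no time-to-event method.

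The Secondary outcomes section lists "v) any minor or major lower limb amputation, vi) all-cause mortality, vii) re-ulceration of the index ulcer, viii) the development of any new ulcers" and, further on, "x) readmission to hospital". None of these is labelled binary by name, but of the two routes given only the binary one can take them. Re-ulceration can only follow healing and is left aside here.

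Follow-up has the same length for everyone: "Recruitment will occur over an 18-month period and participants followed for 12 months". Under Follow up measurements there are visits at 4, 10, 18, 26, 39 and 52 weeks, "with phone consultations every fortnight to determine total" ulcer-free days. Under Adverse events, death and major amputation of the index leg are to be reported promptly to the DSMB.

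**The concern.** For an outcome that is an event, the last observed status before loss means only that nothing had happened by then. Carrying it forward turns this into a statement that nothing happened by month 12. A participant last seen alive and with the limb intact at month 5 enters the 12-month analysis as a survivor without amputation, readmission or new ulcer.

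If loss is unrelated to risk, the error runs one way: the recorded absolute risk is too low. These outcomes carry the trial's evidence on harm and on how long any benefit lasts. The direction also differs from that for healing. Carrying forward an unhealed ulcer works against the arm that loses participants, whereas carrying forward an absence of events flatters it. In an open-label trial, equal loss between the arms cannot be taken for granted.

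**Working it through.** **Inputs from the protocol article**
- Sample size (Study design): 136 needed for 45% v 70% at two-sided 5% and 80% power with continuity correction; 150 to be recruited. The two-proportion formula with that correction gives 68 per arm, 136 in total, so the figure reproduces.
- Loss: no rate is stated. The implied allowance is 1 − 136/150 = 9.3%.
- Mortality (Background): about 50% at 5 years in patients with diabetic foot infections. With a constant hazard, 12-month mortality is 1 − 0.5^(1/5) = 12.9%. This is background, not a forecast for this trial.

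**Assumed inputs**
- 12-month risks of the other events: not given, so a range of 10% to 40% is used.
- Loss of 5% and 20% as alternatives to 9.3%.
- Constant hazards, and loss independent of risk.

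**Formula.** With 12-month event risk R and 12-month loss L, the hazards are h = −ln(1 − R) and c = −ln(1 − L). An event is recorded only if it comes before loss, so the proportion recorded under LOCF is

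h/(h + c) × (1 − exp(−(h + c))).

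**Worked case, R = 30%, L = 9.3%.** h = 0.357, c = 0.098, sum = 0.455. Recorded risk = 0.357/0.455 × (1 − exp(−0.455)) = 28.7%. In relative terms the shortfall is about 4.5%. Among 150 participants this is about 43 recorded events instead of 45.

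**Recorded risk, by true risk and loss**

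| True 12-month risk | 5% loss | 9.3% loss | 20% loss |
|---|---|---|---|
| 10% | 9.8% | 9.5% | 9.0% |
| 12.9% (mortality) | 12.6% | 12.3% | 11.6% |
| 20% | 19.5% | 19.1% | 18.0% |
| 30% | 29.3% | 28.7% | 27.1% |
| 40% | 39.1% | 38.3% | 36.2% |

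The relative shortfall is about 2.5%, 4.5% and 10% in the three columns.

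**Contrast between arms**
- Equal loss of 9.3%: a null effect stays at an odds ratio of 1.00. A true 30% v 20% (10.0 points, odds ratio 1.71) becomes 28.7% v 19.1% (9.6 points, odds ratio 1.70).
- Unequal loss of 5% v 20%, no true difference: the false gap is 12.6% − 11.6% = 1.0 point for mortality, 29.3% − 27.1% = 2.2 points for a 30% event and 39.1% − 36.2% = 2.9 points for a 40% event. In each case the arm with more loss looks safer.
- Milder imbalance, 5% v 13.7%, true 30% in both arms: odds ratio 1.06 or 0.94, depending on which arm loses more.

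**Death as a competing event.** Adding the 12.9% mortality with no loss, an event whose risk would be 30% in the absence of death has a true cumulative incidence of 28.1%, and the yes/no proportion is also 28.1%. Death alone introduces no error. With 9.3% loss added, 26.9% is recorded against 28.1%, so the shortfall again comes from the loss.

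**The case against.** **The effect is small.** This stands. At 9.3% loss in both arms, recorded mortality falls from 12.9% to 12.3%, under one death in 150, and the treatment contrast is almost unchanged. The 1.0 to 2.9 point gaps need an assumed 5% v 20% loss that the document does not support. With 75 per arm, the standard error of a difference at 30% risk is √(2 × 0.3 × 0.7/75) = 7.5 points, so a 2.2-point shift is about 0.3 standard errors. The entry criteria also select people who can be followed for 12 months.

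**Whether the rule includes LOCF is partly inference.** The sentence on secondary outcomes does not repeat LOCF or list the outcomes it covers. The section also names no method for time to full epithelialisation, so it is not a complete list of methods. That is fair. But the sentence refers back to one described method, which includes LOCF, and no other handling of loss is given for binary outcomes. If LOCF was not meant to apply, the text should say so.

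**Stronger readings that the document does not support**
- A reader might infer that participants who die early are also miscounted, so that harms are understated further. A death is an event for all-cause mortality, and no amputation, readmission or new ulcer can follow it. With assumed deaths of 8% v 18% and equal event hazards, recorded risks of 28.9% v 27.4% for a 30% event are the true cumulative incidences; competing-risk curves would return the same values. That difference is a matter of interpretation, not of missed events.
- A reader might infer that a yes/no analysis is wrong in itself. Every participant has the same 12-month horizon, so logistic regression on 12-month status is valid when follow-up is complete.
- A reader might infer that dated information is being thrown away. The stated purpose of the fortnightly calls is ulcer-free days, and serious events reach the DSMB whatever the regression does. The contacts make event timing largely obtainable, but the fault lies in the LOCF rule.

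**Conclusion.** The point holds in a limited form. As written, the rule scores participants lost while event-free as event-free to month 12 for death, amputation, readmission and new ulcers, and so biases their absolute risks down. The shortfall is about 4.5% in relative terms at the implied 9.3% loss and about 10% at an assumed 20%. The comparison between arms is affected materially only if loss is unequal, and then in favour of the arm that loses more.

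These sizes rest on constant hazards, loss independent of risk, assumed event risks and a loss rate inferred from 136 and 150. The bias would be larger if those who leave are at higher risk; the document gives no figure for that. This concerns secondary outcomes and a modest bias, but the rule is stated text and is easily corrected before the analysis.

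**What to change.** In Statistical considerations, Primary and secondary outcomes, exempt death, amputation, readmission and new ulcers from LOCF. Analyse each as time from randomisation to first event, censored at last contact:
- all-cause mortality: Kaplan-Meier curves and a Cox model;
- amputation, readmission and new ulcers: cumulative incidence with death as a competing event, and cause-specific Cox models.

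Keep the 12-month proportions as a descriptive table. Amputation-free survival could be added so that death is not read as limb preservation, but it is optional and not part of the correction.

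The cost is a change of wording, a little more analysis and possibly a software package other than the one named. The visits, calls and event reports already planned should supply most of the timing. Censoring at last contact still assumes non-informative loss, so it would not fully correct for sicker participants leaving.
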